## 5.4 Intervention Modification

Participants will be asked to maintain the assigned intervention throughout the treatment period. In particular, for the tamoxifen arms due to the short time of treatment no dose modification will be applied.

Toxicity will be evaluated using the NCI terminology criteria (CTCAE version 5.0).

If grade 1 or 2 toxicity occurs, the participant will be maintained on treatment irrespective of attribution to the study drug. However, treatment discontinuation should be planned if a persistent/recurrent and intolerable Grade 2 toxicity occurs.

In case of grade 3 toxicity unrelated, unlikely or possibly related to study treatment, participant may remain on treatment as per physician judgment. Women who experience other grade 3 or more severe adverse events will be removed from intervention.

| Toxicity | Attribution to study arm | | | | |
| --- | --- | --- | --- | --- | --- |
| Grade | Unrelated | Unlikely | Possible | Probable | Definite |
| 1 | C | C | C | C | C |
| 2 | C | C | C | C | C |
| 3 | C^1^ | C^1^ | C^1^ | W | W |
| 4 | W | W | W | W | W |

C = Continue intervention; C^1^ = Continue intervention as per physician judgment; W = Intervention withdrawal.

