## 4.2 Exclusion Criteria

1. Diagnosis of ER negative (<10%) DCIS, or history of breast invasive cancer in the previous 5 years;
2. Previous treatment with SERMs or any other hormonal treatment for breast neoplasms;
3. BMI < 18.5 Kg/m^2^ **and/or** Malnutrition Universal Screening Tool (MUST) score ≥2 **and/or** any current or past eating disorders;
4. Any diagnosis of invasive neoplasia, except non-melanoma skin cancer, in the previous 5 years;
5. Any tamoxifen contraindications (abnormal liver function, previous ischemic heart disease, endometrial disorder, previous deep venous thrombosis, history of pulmonary embolus, current or suspected glaucoma, retinopathy and cataract);
6. Current use of warfarin or other anticoagulant drugs
7. Bilateral mastectomy;
8. Pregnancy or desire to become pregnant in the subsequent 9 months after treatment cessation;
9. Diabetes or any other clinical condition that at the investigator’s discretion contraindicates the proposed intervention.
10. No hormonal contraception is allowed during study intervention. Non-hormonal methods will be advised for women of childbearing potential (WOCBP),.

Women must remain abstinent (refrain from heterosexual intercourse) or use non hormonal contraceptive methods with a failure rate of <1% per year during the intervention period and, specifically, from 9 months after the final dose of tamoxifen. A woman is considered to be WOCBP if she is post-menarchal, has not reached a postmenopausal state (>12 continuous months of amenorrhea with no identified cause other than menopause), and is not permanently infertile due to surgery (i.e., removal of ovaries, fallopian tubes, and/or uterus) or other causes determined by the investigator (e.g. Műllerian agenesis). Examples of non-hormonal contraceptive methods with a failure rate of <1% per year include bilateral tubal ligation, male sterilization, and copper intrauterine devices.

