## 5.3.1 Permitted and prohibited medications

The use of tamoxifen in patients receiving dicumarol-type anticoagulant therapy may significantly increase anticoagulant activity; this association must be avoided.

Tamoxifen combination with cytotoxic drugs may increase risk of thromboembolic events episodes this association must be avoided.

Tamoxifen metabolism uses mainly the CYP3A4 and CYP2D6 enzyme. Concomitant medications that interact with these enzymes may result in reduced tamoxifen efficacy. In particular, the combination of tamoxifen and certain SSRI antidepressants or other inhibitor of CYP2D6 (e.g., paroxetine, fluoxetine, quinidine, cinacalcet, or bupropion) should be avoided, since a reduction of tamoxifen efficacy cannot be excluded.

Potentially, any other drug is permitted: participants can take over-the-counter drugs; for drugs prescriptions, participants are asked to inform the investigational staff before treatment initiation.

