## 7.7 Off-Agent Criteria

Participants may interrupt assigned intervention or may stop taking LDT for the following reasons: completed the protocol-prescribed intervention, adverse event or serious adverse event, inadequate agent supply, non-compliance, concomitant medications, medical contraindications, withdrawn consent, positive serum pregnancy test. Participants will continue to be followed, if possible, for safety reasons and in order to collect endpoint data according to the schedule of events. Participants will not be replaced*.*

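### Section 5.4 tells sites to continue tamoxifen through any grade 1-2 toxicity, with no exception by type of event, and is not reconciled with the off-agent reasons in 7.7

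*Protocol*

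**What the plan says.** Protocol 5.4 decides between continuing and withdrawing by CTCAE grade and attribution. For low grades it says: "If grade 1 or 2 toxicity occurs, the participant will be maintained on treatment irrespective of attribution to the study drug". One exception follows: "treatment discontinuation should be planned if a persistent/recurrent and intolerable Grade 2 toxicity occurs". In the accompanying table every grade 1 and grade 2 cell is a plain Continue, across all five attribution columns. Continuation at the physician's judgment is a separate code, used only at grade 3 for events that are unrelated, unlikely or possibly related. The section also states that "for the tamoxifen arms due to the short time of treatment no dose modification will be applied".

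Protocol 7.7 says participants may interrupt the intervention or stop tamoxifen for a list of reasons that includes "adverse event or serious adverse event, inadequate agent supply, non-compliance, concomitant medications, medical contraindications, withdrawn consent". It attaches no grade to the adverse event entry. Section 7.8 gives similar reasons for leaving the study.

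Two other sections show what the protocol regards as incompatible with tamoxifen. The exclusions in 4.2 include "Any tamoxifen contraindications (abnormal liver function, previous ischemic heart disease, endometrial disorder, previous deep venous thrombosis" (item 5, which goes on to list further conditions) and "Current use of warfarin or other anticoagulant drugs" (item 6). Section 5.3.1 says that combining tamoxifen with dicumarol-type anticoagulants "may significantly increase anticoagulant activity; this association must be avoided".

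**The concern.** Grade measures how severe an event is. Whether an event makes tamoxifen unsuitable is a different question. A rule built only on grade and attribution gives the wrong action for an event that is mild on the scale but is itself a reason not to take the drug. The 5.4 exception does not cover that case, because it turns on tolerability: a new contraindication need be neither persistent nor intolerable.

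The stake is the safety of a small number of women. Section 2 names venous thromboembolic events and endometrial cancer as tamoxifen's more serious toxicities, and 2.4 expects no immediate clinical benefit from this phase II trial, so there is little to set against the risk of continuing after such an event. The trial also runs in four centers (section 3). Some may work from 5.4 and others from 7.7, and they could then handle the same event differently.

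**Working it through.** The point is textual, so the sections are set side by side first. Arithmetic is needed only for the reach of the point and the cost of the fix.

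**Step 1: what 5.4 leaves open at grades 1-2.** Two grade rows times five attribution columns give 10 cells, and all 10 are an unqualified Continue. Dose modification is ruled out in the tamoxifen arms. Outside the intolerable grade 2 exception, 5.4 on its own therefore offers one action, which is to continue the assigned 10 mg every other day. It gives the physician less stated discretion at grades 1-2 than at grade 3.

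**Step 2: what 7.7 adds.** Its wording is permissive (participants may stop), it covers adverse events without a grade, and it lists concomitant medications and medical contraindications as separate reasons. For a low-grade event that contraindicates tamoxifen, 5.4 says continue and 7.7 allows a stop without requiring one. Neither section refers to the other, and no order of precedence is given.

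**Step 3: an illustration.** Suppose a woman in Arm 1 or 2 has a new venous thrombosis that is graded 1 or 2. Had it come before entry, it would have excluded her under 4.2 item 5, and treating it would have excluded her under item 6. Those items govern entry only; they are used here to show what the protocol treats as a contraindication. On study, 5.3.1 names only dicumarol-type anticoagulants among the anticoagulants to be avoided and then says "Potentially, any other drug is permitted: participants can take over-the-counter drugs", adding that participants should tell staff before starting a prescribed drug. With another anticoagulant, 5.3.1 would not by itself stop tamoxifen. Section 5.2 might, since it disallows medications that may affect participant safety, but 5.4 does not refer to it.

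**Step 4: can the event be low grade?** The protocol gives no event-specific grades. On the general scale in 10.1, grade 2 includes a need for noninvasive intervention and grade 3 includes medically significant events. The grade of such a thrombosis is therefore open.

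**Step 5: reach.** 200 women randomized 1:1:1:1 give 50 per arm, so 2 × 50 = 100 in Arms 1 and 2. The protocol gives no rate for low-grade contraindicating events. As an assumption only, 0% to 5% of 100 is 0 to 5 women.

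**Step 6: cost of stopping more women.** Inputs from 12.1: 90 per group, SD 35 nmol/L, difference 15 nmol/L, two-sided alpha 5%, two-sample t-test. The standardized difference is 15/35 = 0.429 and the noncentrality is 0.429 × √(90/2) = 2.87 on 178 degrees of freedom. Power is 81.6%, in line with the planned 80%. In the worst case every additional woman who stops loses the whole effect, so the difference becomes 15 × (1 − k) for a stopping proportion k:

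| k (assumed) | Difference (nmol/L) | Power |
| --- | --- | --- |
| 0% | 15.00 | 81.6% |
| 1% | 14.85 | 80.8% |
| 2% | 14.70 | 80.0% |
| 5% | 14.25 | 77.5% |

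Power reaches exactly 80% at a difference of 14.70 nmol/L, which is k = 1 − 14.70/15, about 2.0%.

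**The case against.** The strongest reply is that the sections do not conflict. Section 5.4 is a toxicity rule, while 7.7 is the trial-wide list of reasons to stop and treats contraindications and concomitant drugs as grounds separate from adverse events. Read together, low-grade toxicity alone does not end treatment, but a contraindication can. That reading is available, and it removes the stronger inference a reader might draw, that the two sections directly contradict each other or that the protocol has no exit. Sections 7.7 and 7.8 both supply one. A reader might also take 7.7 to say that an adverse event of any grade is enough; it states no grade, so that would be inference.

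Other text also weakens the idea that sites would keep contraindicated women on the drug. Section 5.2 disallows medications that may affect safety. Section 5.3.1 asks women to report prescriptions before starting them. Section 10.1 requires clinically significant events to be followed by good medical practice. A thrombosis that meets the SAE definition in 10.2 is reported within 24 hours, and a serious adverse event is a listed reason to stop in 7.7. The protocol also refers sites to the tamoxifen SmPC, which is not available here and may instruct on this. A thrombosis may be graded 3, where 5.4 allows judgment or requires withdrawal if the event is probably or definitely related. The regimen is low dose, and section 2 reports no excess of endometrial cancer, DVT or pulmonary emboli at 5 mg per day.

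All of this limits the size of the point. It does not change the fact that 5.4 is worded as mandatory, that 7.7 makes stopping only optional even for a true contraindication, and that the section addressing toxicity decisions sends nobody to the others.

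**Conclusion.** The point holds as a minor, unreconciled rule. For a grade 1-2 event that contraindicates low-dose tamoxifen, 5.4 taken literally gives the wrong action, and the protocol does not say that 7.7 overrides it. A related slip inside 5.4 is that the grade 2 row of the table omits the exception stated in the text above it.

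The size is small. Of about 100 women on tamoxifen, few and possibly none would be affected; the 0 to 5 range rests on an assumed rate. The conclusion assumes that a contraindicating event can be graded 1-2, which the protocol neither shows nor rules out. Low-grade liver enzyme rises and minor endometrial findings may reasonably be continued and are not part of the point. The documents do not support a claim that women will in practice be kept on a contraindicated drug, and no bias in the SHBG comparison is claimed. Confidence is medium.

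**What to change.** Add to the 5.4 text, and as a footnote to its table: *In Arms 1-2 the grade 1-2 Continue rule is subject to 5.2, 5.3.1 and 7.7. Tamoxifen is stopped, whatever the grade, for a new venous thrombosis or embolism, for another clinically significant tamoxifen contraindication as judged by the investigator, or when the event requires a drug that must be avoided with tamoxifen and cannot be substituted. Endpoint follow-up continues under 7.7.* Mark the persistent or recurrent, intolerable grade 2 exception in the table as well. Section 7.7 needs no change, and there should be no automatic stop for minor endometrial findings or low-grade liver enzyme rises.

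The cost is a short amendment, with no extra data, visits or participants. The downside is a few more discontinuations. The worst-case power loss in the table above is an upper bound, because some of these women would stop under 7.7 anyway. Those who stop are still followed where possible (7.7) and remain in the intention-to-treat analysis (12.3).

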## 5.5 Adherence/Compliance

To be compliant, a participant has to take ≥ 75% of the scheduled pills and/or follow 75% of the expected days of intermittent caloric restriction as per assigned arm. We propose the use of multiple methods of adherence monitoring: subject self-reporting, diary completion and tablets count.

*Diary completion*: All participants will receive at each visit a calendar to facilitate tracking and recording of protocol treatment (Appendix C). Each participant will be asked to mark or write Yes/No in the corresponding day of the diary. Based on treatment assignment, participants are asked to fill the diary and some additional space will be left for participant’s notes.

A total of 120 pills will be supplied in Arms 1 and 2. Each participant will be asked to return all full and empty blisters.

Should the tablets not be returned, compliance will be calculated from the diary only.

Participants on Arms 2 and 4 will be asked to mark yes/no in the corresponding dates of ICR.

Participants on Arms 3 and 4 will be asked to record the step count number on a weekly basis.

An according-to-protocol subgroup analysis will be restricted to women who are “compliant”, such as participants who have taken ≥ 75% of the pills, for those randomized to tamoxifen and ≥ 75% of the days with the respected caloric restriction, by the reported diary

# 6. PHARMACEUTICAL INFORMATION

## 6.1 Name of experimental drug

Generic name: Tamoxifen

Chemical name: (z)-2-[4-(1,2-Dyphenyl-1-butenyl)phenoxy]-N,N-dymethylethanamine

Product classification: non-steroidal estrogen antagonist

CAS Registry No: 10540-29-1

Molecular formula: C26H24NO

Molecular weight: 371.53

Key chemical characteristics: fine, white odorless crystalline powder, mp 140-142°C. Slightly soluble in water, soluble in methanol, ethanol, acetone. Hygroscopic at high relative humidities.

Tamoxifen tablets: tamoxifen citrate, lactose, maize starch, hypromellose, magnesium stearate, sodium glycolate starch, macrogol 300, titanium dioxide.

## 6.2 Reported Adverse Events and Potential Risks

The most commonly reported adverse events (AEs) by early breast cancer patients treated with tamoxifen were (in order of frequency): hot flushes, sweating increased, gynecological disorders, insomnia, and dizziness., musculoskeletal disorders (in particular cramps), peripheral edema, pruritus, reduction in bone mineral density in premenopausal women. At hematological/biochemistry level, leucopenia, lymphocyte count decreased, and liver enzymes increase. A detailed list of adverse events and their frequencies is reported in the Tamoxifen SmPC given at 20 mg/day dose.

## 6.3 Availability

Tamoxifen tablets will be purchased, packed and labeled by the

IEO Pharmacy

[name]

[name]

Director: [name]

Each box will report Study number, PI name, and expiring date.

## 6.4 Agent Distribution

The IEO Pharmacy department will be responsible for investigational drug distribution. [name], as PI of the study and the local Site Investigators or their designees will be responsible for drug administration. They can delegate other study investigators (MDs and research nurses) to distribute the agent on their behalf.

## 6.5 Agent Accountability

The Investigator, or a responsible party designated by the Investigator, must maintain an updated record of the inventory and disposition of all agents received from IEO pharmacy. The Investigator is required to maintain adequate records of receipt, dispensing and final disposition of study agent. This responsibility has been delegated to the local pharmacist*.* Include on receipt record from whom the agent was received and to whom study agent was shipped, date, quantity and batch or lot number. On dispensing record, note quantities and dates study agent was dispensed to and returned by each participant.

## 6.6 Packaging and Labeling

Commercially available 10 mg Tamoxifen will be re-packaged and labeled according to EU Regulation 536-2014 article 61 par.5. Drug boxes will be distributed by IEO Pharmacy to each Institutional Pharmacy.

Tablets will be packaged in blisters. A two-part label will be used, 1 tear-off remains on the box, 1 tear-off on the source document (Appendix D).

The fixed part of the label will remain attached to the box and will identify the following:

Tamoxifen 10 mg: 120 Tablets

Expiration Date: XX-XX-XXXX

Study Number:

Patient ID: _________________________

Dispensed Date: _____________________

Take one tablet every other day at the same time.

Store at Controlled Room temperature 15°C - 25°C

Keep Out of Reach of Children

CAUTION: DRUG – LIMITED TO INVESTIGATIONAL USE ONLY

## 6.7 Storage

Study drug will be stored in a secure location at controlled room temperature, with excursions permitted between l5°-25°C at each Institutional Pharmacy*.*

## 6.8 Agent Destruction/Disposal

At the completion of investigation, all unused study agent will be returned and disposed by the local Institute Pharmacy.

# 7. CLINICAL EVALUATIONS AND PROCEDURES

## 7.1 Schedule of Events

The possibility of taking part to this trial will be presented to all the eligible mutation carriers followed in our clinics, or to women with a 10 years BC risk >5% by Tyrer-Cuzick model, or patients with a diagnosed ER-positive DCIS or any LCIS or ADH after standard surgery. The schedule of events at each time point is reported below.

**SCHEDULE OF EVENTS**

| Evaluation/ Procedure | T0  Screening Visit  Days -30-1 | T1  Baseline Visit/Randomization  Day 0 | T2  Phone call/ teleconsulting  (within 1 month) | T3  Phone call/ teleconsulting  (2 months) | T4  Visit  (3 months) | T5  Phone call/ teleconsulting  (5 months) | T6  Final Visit  (6 months) |
| --- | --- | --- | --- | --- | --- | --- | --- |
| Informed Consent | X |  |  |  |  |  |  |
| Stool Collection kit | X |  |  |  | X |  |  |
| Assess eligibility | X | X |  |  |  |  |  |
| Medical history |  | X |  |  |  |  |  |
| Physical exam/ anthropometric measures and body composition (BIVA) |  | X |  |  | X |  | X |
| Tobacco/alcohol use assessment |  | X |  |  |  |  |  |
| Fasting blood collection^a-b^ |  | X^b^ |  |  | X |  | X^b^ |
| Gravindex |  | X* |  |  |  |  |  |
| Stool collection |  | X |  |  |  |  | X |
| Mammography (according to Institutional guidelines)^c^ |  | X |  |  |  |  | X |
| Body fat composition (DEXA)^d^ |  | X |  |  |  |  | X |
| Concomitant medications |  | X |  |  | X |  | X |
| Baseline Symptoms |  | X |  |  |  |  |  |
| Randomization |  | X |  |  |  |  |  |
| Nutrition counseling |  | Arms 2, 4 only | Arms 2, 4 only | Arms 2, 4 only | Arms 2, 4 only | Arms 2, 4 only |  |
| Physical activity counseling |  | Arms 3, 4 only | Arms 3, 4 only | Arms 3, 4 only | Arms 3, 4 only | Arms 3, 4 only |  |
| Tamoxifen safety |  |  | Arms 1, 2 only | Arms 1, 2 only | Arms 1, 2 only | Arms 1, 2 only | Arm 1, 2 only |
| WCRF recommendations | X | X |  |  |  |  |  |
| Collect study agent |  |  |  |  |  |  | X |
| Compliance |  |  | X^g^ | X^g^ | X^e^ | X^g^ | X^e^ |
| Review diary |  |  |  |  | X |  | X |
| Adverse events |  |  | X | X | X | X | X |
| Study Questionnaires: QoL, DIET and IPAQ | X^f^ | X |  |  | X |  | X |

* In women of childbearing potential only

a. Glycemia will be measured locally and blood specimen will be collected for biomarkers as per Manual of procedure

b. Additional blood collection in dedicated tubes for RNA extraction as per Manual of procedure.

c. Mammogram will be performed only in a subgroup of participants based on their age and center guideline, and can be within 6 or 12 months from baseline visit depending on disease status.

d. In a subgroup of participants only, depending on local availability.

e. Revision of diary completion only. Unused and/or empty blisters will be returned at month 6 visit arms 1,2

f. 3-day food records only

g. Compliance with Intermittent Caloric Restriction

## 7.2 Pre-study screening visit

During the screening visit, the health care professional will illustrate the aim and the trial procedures to the candidate and eligibility will be assessed. If the woman wishes to consider to participate, she will be asked to sign the informed consent. We will provide her the stool collection kit and instruct her about baseline sample collection. The baseline visit will be scheduled within 30 days.

Information on dietary habits will be obtained to facilitate personalized consultation sessions.

## 7.3 Baseline

Baseline evaluations are:

Fasting glycemia and blood collection for circulating biomarkers; stool sample collection. Date of last menses will be recorded. Physical exam and medical history, vital signs, alcohol and tobacco assessment, anthropometric measurement (height, weight, waist measurement, hip measurement), body composition (BIVA), quality of life assessment; food consumption and level of physical activity enquired through self-administered questionnaires as explained below. Gravindex test will be obtained in women of childbearing potential.

The use of concomitant medications and any baseline symptom will be recorded.

At baseline, participants will be instructed about the importance of drug compliance, and lifestyle recommendation/instruction based on the randomization arm.

Participants will be provided and instructed on how to fill-up the calendar that will be dated and signed.

Participants will be informed that a pill count will be conducted on their study medication use so that their study medication blisters with remaining tablets must be returned at the clinic visit.

**STUDY QUESTIONNAIRES**

Quality of life will be assessed using the self-administered MenQoL questionnaire (Mapi Research Trust, France) during all visits. This tool is based on 29 items divided into four domains (vasomotor, physical, psychosocial, and sexual). Each item is scored from 1 to 8: 1 means no symptom, 2 indicates presence of the symptoms but not bothersome, 3 to 8 mean an increasing grade of discomfort. The vasomotor domain includes three items to investigate hot flashes and sweating. In the physical domain, there are 16 items covering general symptoms, skin, gastrointestinal, sleeping problems, and urinary symptoms. The psychosocial domain includes seven items, evaluating states of anxiousness, memory, and loneliness. The sexual domain has three items: sexual desire, vaginal dryness, and avoiding intimacy (see Appendix E).

